### Inclusion criteria

2.3

EC without esophagogastric junction pT_1-4a_N_+_M_0_ (stage IIB-IVA) that met the diagnostic criteria without recurrence or distant metastasis;Patients who completed adjuvant therapy (including adjuvant radiotherapy, chemotherapy, chemotherapy + radiotherapy) within 6 months after R0 resection for EC.ECOG score 0–2.18–75 years old.Expected survival ≥ 3 months.Participants who voluntarily signed informed consent.

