### Sample size calculation

2.9

This study is a RCT. The test group was administered QZYLP Granules, while the control group was placed on a placebo. The primary outcome measure was the postoperative DFS of patients. The study was designed as a superiority trial with a 1:1 ratio between the test and control groups. According to the literature, the mDFS for patients with lymph node-positive esophageal squamous carcinoma after surgery with adjuvant therapy is 19.3 months (19). Assuming that the DFS of the test group was 12 months longer than that of the control group, with α=0.05 and 1-β=0.80, the expected time to enroll all participants was 24 months, and the total duration of the clinical trial was expected to be 36 months, with a consistent enrollment rate of the study participants. Using PASS 11 software, it was calculated that 140 cases were needed in each of the test and control groups. Considering a 10% dropout rate, 155 participants were enrolled in the test and control groups, resulting in a final number of 310 participants. The following formula was used (20). Here δ=π_1_-π_2_.

$$n={\left(\frac{u_{\alpha }+u_{\beta }}{\delta }\right)}^{2}[\pi_{1}(1-\pi_{1})+\pi_{2}(1-\pi_{2})]$$

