### Statistical analysis

2.14

Statistical software: SAS 9.4 statistical software will be utilized to analyze effective indicators using the Full Analysis Set and Per Protocol Set analyses. A safety data set analysis will be performed for adverse reactions.

Statistical methods: All statistical tests will be two-sided, with *P*≤ 0.05 considered statistically significant for the differences tested. Data will be analyzed for outliers, which are professionally evaluated to determine appropriate trade-offs. Missing values will also be professionally analyzed to determine whether to classify them as dropouts or data transfers. The proportion of missing cases should not exceed 10%; otherwise, they should be analyzed and explained. Measurement data will be described using mean, standard deviation, median, minimum, and maximum values. Count data will be described using frequency and percentage. The *T*-test and rank-sum test, among others, will be employed to analyze measurement data, while the chi-square test and Ridit analysis will be used for count data. Survival data will be analyzed using the Kaplan–Meier method, Wilcoxon rank-sum test, and log-rank test. For multifactorial survival analysis, the Cox proportional risk regression model will be used. To reveal whether there are differences in effects between different feature groups, subgroup analyses will be performed on subgroups for sex, age, occupation, health status (smoking, alcohol using, hypertension, diabetes, etc), type of operation, and adjuvant therapies.

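### No test is named as decisive for the primary 1-year DFS rate, and pathological stage is named neither in the main comparison nor among the subgroups

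*Protocol article*

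**What the plan says.** Sections 2.1 and 2.11.1 of the protocol article make the primary endpoint a proportion: patients alive and free of relapse 1 year after surgery. Section 2.11.2 lists DFS time, counted from randomization, as a secondary outcome. Section 2.9 calls the primary measure postoperative DFS and sizes the trial from a median.

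Section 2.14 assigns methods by type of data. For counts: "the chi-square test and Ridit analysis will be used for count data". For survival: "Survival data will be analyzed using the Kaplan–Meier method, Wilcoxon rank-sum test, and log-rank test". The significance limit is P ≤ 0.05 ("All statistical tests will be two-sided"), and efficacy is analysed in both the full analysis set (FAS) and the per-protocol set (PPS). A Cox model is also planned for multifactorial survival analysis, without a list of covariates. No test and no analysis set is marked as decisive.

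On subgroups, section 2.14 says: "To reveal whether there are differences in effects between different feature groups, subgroup analyses will be performed". The list then runs through demographic factors including occupation, habits and comorbidities, type of surgery and adjuvant treatment. Stage is not in it. Section 2.3 admits node-positive patients ("stage IIB-IVA) that met the diagnostic criteria without recurrence or distant metastasis"), so stage varies widely and is established before randomization. Section 2.6 names centre and patient identifiers as examples of what is entered for randomization, and the Discussion claims balance across sub-centres. No prognostic factor is mentioned in either place.

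**The concern.** A 1-year DFS rate can be compared as a count (chi-square) or through the survival curve (log-rank, Wilcoxon). The article makes all of these available at the same level and ranks none of them. If they disagree, nothing in it settles which one is the trial's answer, and a reader cannot rule out that the test was chosen after the result was seen.

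Stage raises a separate question, one of efficiency. In a stage IIB–IVA population it is an obvious candidate for a strong prognostic factor. The named tests are unadjusted, and if stage is strongly prognostic, an unadjusted comparison gives up power that a stratified one would keep. Leaving stage out of a list detailed enough to include occupation also means that the subgroup contrast a clinical reader is most likely to ask for is not planned. Finally, the article wants to show differences in effect between subgroups but does not say how such a difference will be judged.

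**Working it through.** **1. Reproducing the planned size.** Inputs from section 2.9: "α=0.05 and 1-β=0.80"; control median ("the mDFS for patients with lymph node-positive esophageal squamous carcinoma after surgery with adjuvant therapy is 19.3 months"); effect ("Assuming that the DFS of the test group was 12 months longer than that of the control group"); 24 months of uniform accrual; 36 months in total; 1:1 allocation. Two-sided testing is from section 2.14. Exponential survival is assumed.

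- Test-arm median 19.3 + 12 = 31.3 months; HR = 19.3/31.3 = 0.617.
- Events (Schoenfeld) = 4(1.960 + 0.842)²/(ln 0.617)² = 134.3, rounded up to 135.
- Event probability per arm = 1 − [exp(−12λ) − exp(−36λ)]/(24λ), with λ = ln 2/median. This gives 0.564 (control) and 0.405 (test), mean 0.485.
- n per arm = 134.3/(2 × 0.485) = 138.5. Lachin–Foulkes gives 142.8 and Freedman 143.9. The stated 140 is reproduced.

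The two-proportion formula printed in section 2.9, with the same exponential curves, gives 139.5 per arm at 24 months (0.423 v 0.588). At 12 months (0.650 v 0.767) it gives 234. Either way, 140 rests on the median DFS assumption and not on a 12-month comparison.

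**2. Type I error if any significant test counted as success.** Simulated with 280 patients under the design above and no treatment effect. There were 20,000 trials for each of four assumed stage effects; the standard error near 5% is √(0.05 × 0.95/20,000) = 0.15 points.

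- Log-rank alone 5.0–5.4%; Wilcoxon (Gehan) alone 4.9–5.1%; chi-square on 12-month status alone 5.0–5.2%.
- Log-rank or Wilcoxon: 6.5–6.9%.
- Any of the three: 8.4–8.8%. A separate run of 12,000 trials gave 6.7% and 8.9%.
- Independent tests would give 1 − 0.95² = 9.8% and 1 − 0.95³ = 14.3%. The actual figures are lower because the tests are correlated.

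The unadjusted log-rank test stays at about 5% for every stage effect tried, so leaving stage out does not inflate type I error.

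**3. The choice of test matters under the planned effect.** With HR 0.617 and no stage effect (10,000 trials), power is 80.2% for log-rank, 75.2% for Wilcoxon and 57.9% for a 12-month chi-square.

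**4. Power given up by leaving stage out.** Assumed, because the documents give no figures: three stage groups of 20%, 50% and 30%, a constant hazard ratio per step, treatment HR 0.617 within stage, and the control median held at 19.3 months. There were 10,000 trials per row; the standard error is about 0.4 points.

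| Stage HR per step | Unadjusted log-rank | Stage-stratified log-rank | Gain |
|---|---|---|---|
| 1.0 | 80.17% | 79.48% | −0.69 |
| 1.5 | 77.03% | 78.58% | 1.55 |
| 2.0 | 74.48% | 79.88% | 5.40 |
| 2.5 | 70.23% | 79.65% | 9.42 |

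The last row implies 2.5² = 6.25 between the extreme groups, which is a strong assumption. With two equal stage groups and hazard ratios of 2, 2.5 and 3, unadjusted power is 77%, 76% and 73%, against 80–81% stratified.

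**5. Subgroups.** Suppose the same HR of 0.617 holds in both levels of a factor and about 135 events are split 50:50. Power in each level is then about 51%, so the two levels disagree on significance in 2 × 0.51 × 0.49 = 50% of trials. With a 70:30 split (65% and 34%) it is 55%; with 80:20 (71% and 24%) it is 61%. These figures apply only if subgroups are read by significance within each level.

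**Simplification.** The 12-month status in steps 1 to 3 is counted from the start of the exponential curve, that is, from randomization. The article counts the year from surgery, and patients enter after adjuvant therapy. The chi-square figures are therefore approximate for the stated endpoint.

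**The case against.** The best defence is that the tests belong to different endpoints: chi-square for the primary proportion, log-rank and Wilcoxon for the secondary DFS time. On that reading there is one primary test and no competition. It is a natural reading, but the article does not state it, and section 2.9 describes the primary measure as DFS and sizes the trial from a median. The gap remains.

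Several stronger readings are tempting and do not stand:

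- **Three rival tests in the quoted sentence.** It names two; Kaplan–Meier is an estimator. The third comes from the sentence on count data.
- **A type I error of 8–9% in this plan.** Nothing says that any one significant test is enough. The figure shows what an open choice could cost.
- **Stage is never used.** The planned Cox model has unlisted covariates that may include stage, and an article may leave that list to the full protocol or SAP. The text supports only that stage is not named.
- **FAS and PPS as two chances of success.** Reporting both is routine and does not imply this.
- **The subgroup plan will produce false claims.** The stated aim is compatible with interaction tests. The 50–61% figures assume a rule that the article does not give.

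The size of the power loss rests on assumed stage effects and was computed for DFS time, not for the 1-year rate. Leaving stage out of the subgroup list costs the primary comparison no power.

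**Conclusion.** The point holds in a limited form. The article names several tests at the same level without saying which decides the primary 1-year DFS rate, and it names stage neither in the main comparison nor in an otherwise detailed subgroup list.

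The two consequences should be kept apart. The open choice of test could raise type I error from 5% to about 6.5%, or to 8–9% with chi-square, but only if any significant result were accepted. Leaving stage unadjusted keeps type I error at about 5% and costs the log-rank test roughly 0 to 10 power points for assumed hazard ratios of 1.0 to 2.5 per step. A reader might infer that the missing stage variable also inflates false positives; the simulation shows that it does not.

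This should be corrected before unblinding, but it does not invalidate the design. If an SAP that is not shown already names the deciding test and adjusts for stage, what remains is to bring the protocol into line and add stage to the subgroups.

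**What to change.** Before unblinding:

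- Name one FAS analysis as decisive for the primary endpoint, stratified or adjusted for pathological stage. With the endpoint as now defined, that could be a stage-stratified comparison of the 1-year DFS rate, accompanied by a stage-stratified log-rank test and a stage-adjusted Cox hazard ratio for DFS time. Fix the stage grouping in advance.
- Label the unadjusted, Wilcoxon and PPS results as supportive.
- If a log-rank test of DFS is preferred as primary because the 140 per arm was derived from median DFS, do not make that change by analysis wording alone. Sections 2.1 and 2.11.1 (1-year rate from surgery), 2.9 (median DFS) and 2.11.2 (DFS time from randomization, secondary) must first be reconciled by a documented amendment.
- Add stage to the subgroup list. Judge differences in effect by treatment-by-subgroup interaction, show hazard ratios with 95% confidence intervals, and label the subgroup analyses exploratory.

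The cost is a protocol and SAP amendment and slightly more analysis work. No new data are needed, because stage is established at eligibility. If stage turns out to have no prognostic effect, stratifying costs under one power point in the scenario computed.

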### Quality control

2.15

To protect the rights and interests of the participants, the investigator will comply with the *The International Council for Harmonization (ICH) ICH-E6 Good Clinical Practice (GCP)* (23), ensuring the scientific validity, reliability, accuracy, and completeness of the study.

#### Quality control

2.15.1

The principal investigator (PI) is responsible for the overall quality control of the study, which is specifically implemented and executed by individual investigators and other participants. This included: ① Regularly verifying the operation of the postoperative EC case registry platform. ② Ensuring all investigators adhering strictly to standard operating procedures and trial protocols. ③ Recording clinical data in a timely, direct, accurate, and clear manner, including signatures and dates. ④ Frequently self-checking the accuracy and completeness of data records and using prescribed methods to correct errors. (5) Using validated and reliable statistical software for data analysis. (6) Implementing effective quality control measures for data entry, such as double entry.

#### Monitor

2.15.2

Individuals are appointed by the PI to oversee the entire clinical trial. Their responsibilities included the following: ① Before the trial: selecting investigators, assisting in the development of trial documents, preparing trial materials, and organizing investigator meetings; ② During the trial: conducting regular monitoring, managing and supplying trial materials, monitoring trial progress and confirming informed consent is obtained, ensuring investigators comply with the trial protocol, verifying original information and regularly accessing trial documents, managing the trial drug and storing the blinding code, recording and reporting adverse events, and timely submission of monitoring reports to the PI; ③ At the end of the trial: conducting a final visit, recovery of trial materials, preserving trial data, and assisting the investigator in reporting trial results to the PI.

#### Audit

2.15.3

Clinical trial PIs should engage a quality assurance department or a third party to conduct audits. The auditor will be independent of the clinical trial. The main responsibilities include reviewing the original trail information and reports, conducting internal and external audits, maintaining relevant documents, and offering guidance and training to investigators and those monitoring the trails.

### Ethical approval and confidentiality

2.16

The study was approved by the Medical Ethics Committee of Guang’anmen Hospital, CACMS (2022-200-KY-01), and will be conducted under its supervision. All participants will provide written informed consent before enrollment to ensure voluntary participation. Laboratory samples, reports, and data collection will be identified by code instead of the names of participants. All study-related paper materials will be securely stored in locked file cabinets to protect the confidentiality of the personal medical information of the participants.

## Discussion

3

Currently, EC has caused a huge medical burden, and the OS benefit is still limited in spite of the advances in surgical techniques and optimization of radiotherapy regimens (24). The reason is that metastasis is still the Achilles heel of radical surgery for EC. The phase III trial NEOCRTEC5010 (25) shows that the overall recurrence rate after radical esophagectomy for locally advanced ESCC was 45% (159/353). Recurrence mainly occurred within 2 years after surgery (71.7%; 114/159).

How to overcome postoperative recurrence and metastasis has become a clinical challenge. In this context, TCM has great potential as a complementary therapy to current mainstream medicine. In previous studies of TCM interventions for EC, the outcome indicators primarily focused on short-term efficacy, such as quality of life and attenuation of adverse effects (26, 27). The participants were mostly in the middle to late stages of EC, and the effects of TCM were evaluated primarily when used as adjuvant therapy alongside radiotherapy or chemotherapy (28). A systematic review by Chen X et al. (11) included nine RCTs examining the clinical outcomes of TCM in treating patients with EC undergoing radiotherapy and chemotherapy. The results showed that the combined use of TCM positively influenced quality of life and increased patient tolerance to side effects caused by radiotherapy or chemotherapy. In terms of postoperative survival, a previous study on TCM focusing on OS and DFS in postoperative EC demonstrated that combining chemotherapy with TCM reduced the 3-year recurrence and metastasis rate by 23.3% and increased the 3-year survival rate by 14.1% compared with that of chemotherapy alone. It also significantly improved the quality of life and immune function of patients (29). However, a single-center, open-label design with incomplete randomization of the allocation sequence was employed in this study, which may not fully mitigate selectivity and implementation biases. Therefore, whether TCM alone improves the long-term prognosis of postoperative patients with EC still needs high-quality evidence to demonstrate.

This double-blind, multicenter, randomized, placebo-controlled clinical trial holds significant importance in investigating TCM as a complementary therapy to prevent recurrent metastasis after EC surgery. The advantages of this study are as follows: ①Central and block randomization was performed using the IWRS to ensure concealed allocation to balance unmeasured confounders. This approach maintained balanced non-experimental factors across multiple sub-centers competing for enrollment (30). ②Participants, care providers, investigators, and outcomes assessors were blinded to avoid placebo effect, information bias, and implementation bias, thereby obtaining more realistic trial data (31). ③The intervention timing was set at the end of postoperative adjuvant therapy, thereby eliminating the influence of confounding factors other than necessary symptomatic treatment on the outcome. ④The sub-centers of this study are primarily located in eastern China, where EC is highly prevalent, and the population is mainly Han Chinese (32). It is more typical and representative to evaluate the efficacy of QZYLP, while one limitation is that assessing other ethnic groups and regions will not be possible.

The main intervention measure of this study, QZYLP granules, was developed by Guang’anmen Hospital after extensive clinical practice and research. According to the theory of TCM, the occurrence and progression of EC are closely related to the pathological factors of phlegm and qi (33). Previous studies have shown that the obstruction of phlegm and qi are main factors affecting the recurrence and metastasis of EC after operation(*P*=0.019, *P*=0.016) (34). QZYLP is a targeted prescription of phlegm and qi in the postoperative patients with EC. It exhibits pharmacological action characterized by multi-element, multi-system, multi-target, and multi-mechanism effects. The primary components of QZYLP, such as *Astragali Radix* (35), *Codonopsis Radix* (36), and *Rhizoma Atractylodis Macrocephalae* (37), possess anticancer and immunomodulatory properties. Network pharmacology studies (38) showed that the potential targets of QZYLP interacted with multiple signaling pathways. One of the main roles was the regulation of oxidative stress. Phospholipids and cholesterol esters in cell membranes and lipoproteins readily reprogram lipid metabolism through the process of lipid peroxidation (39), which can alter the tumor microenvironment (TME) to promote tumor progression. Lipid accumulation impairs CD8^+^T-cell function in the TME and accelerates tumor growth (40), or enhances regulatory T-cell functional specialization in the TME (41). These processes eventually lead to immunosuppression and the progression of EC. In addition, our pre-metabolomics studies have found differences in the abundance of lipid metabolites in peripheral blood after QZYLP intervention. Therefore, we chose secondary outcome indicators related to lipid distribution and immunomodulation in order to elucidate the mechanism of action of QZYLP in biological terms.

To sum up, this study aims to further clarify the efficacy and safety of QZYLP in preventing postoperative recurrence and metastasis of EC, and to explore the mechanism of action. The results of this study will provide high-quality evidence for the participation of TCM in the comprehensive treatment program of EC, and improve the precise diagnosis and treatment system of TCM in EC. At the same time, the transformation of TCM will promote the clinical application, prolong the survival time, and enhance the benefit of patients in the future.

## Trial status

4

The trial was prospectively registered at Clinical Trials. gov (ID: NCT05626309) on November 19,2022. Recruitment began in October 1,2022. Expected date when recruitment will be completed in August 30,2024. Due to COVID-19, the recruitment completion date will be extended.

## Data Availability

The original contributions presented in the study are included in the article/**Supplementary Material**. Further inquiries can be directed to the corresponding authors.
